## Abstract

A common problem in the older population is the risk of falling and related injury, immobility, and reduced survival. Age-related neuronal changes, e.g., decline in gray-and white-matter, affect neuronal, cognitive, and motor functioning. The improvement of these factors might decrease fall events in elderly. Studies showed that administration of video game-based physical exercise, a so-called exergame, or omega-3 fatty acid (FA) may improve motor and/or cognitive functioning through neuronal changes in the brain of older adults. The aim of this study is to assess the effects of a combination of exergame training with omega-3 FA supplementation on the elderly brain. We hypothesize that an intervention using a combination approach differently affects on the neuronal structure and function of the elderly's brain as compared to the sole administration of exergame training. The study is a parallel, double-blinded, randomized controlled trial lasting 26 weeks. Sixty autonomous living, non-smoking, and right-handed healthy older (>65 years) adults who live independently or in a senior residency are included, randomized, and allocated to one of two study groups. The experimental group receives a daily amount of 13.5 ml fish oil (including 2.9 g of omega-3 FA), whereas the control group receives a daily amount of 13.5 ml olive oil for 26 weeks. After 16 weeks, both groups start with an exergame training program three times per week. Measurements are performed on three time-points by treatment blinded investigators: pre-intervention measurements, blood sample after 16 week, and post-intervention measurements. The main outcomes are motor evoked potentials of the right M. tibialis anterior (transcranial magnetic stimulation) and response-related potentials (electroencephalography) during a cognitive test. For secondary outcomes, reaction time during cognitive tests and spatio-temporal parameters during gait performance are measured. Statistics will include effect sizes and a 2 × 2-ANOVA with normally distributed data or the non-parametric equivalent for data not fulfilling normal distribution. The randomized controlled study is the first to investigate the effectiveness of exergame training combined with omega-3 FA in counteracting age- and behavioral-dependent neuronal changes in the brain. This study has been registered in the Swiss National Clinical Trials (SNCTP000001623) and the ISRCTN (ISRCTN12084831) Portals.

## Introduction

In general, the human brain undergoes age-dependent changes by losing about 15% of the cerebral cortex and about 25% of the cerebral white-matter between the ages of 30 and 90 years (Colcombe et al., 2003). Age-associated alterations in gray-matter and white-matter integrity (Longstreth et al., 1996; Gunning-Dixon et al., 2009; Fjell and Walhovd, 2010) and a decrease in synthesis and binding of dopamine (produced in substantia nigra and ventral tegmental area), serotonin (produced in raphe nuclei), and acetylcholine (produced in pedunculopothine nucleus and laterodorsal tegmental nucleus, medial septal and diagonal band nuclei, and nucleus basalis; Wang et al., 1995, 1998; Volkow et al., 1998; Bäckman et al., 2006; Schliebs and Arendt, 2011) are connected to deteriorations of cognitive functioning, e.g., working memory and executive function (EF). EFs are interrelated cognitive abilities that control and guide goal-directed actions (Banich et al., 2009); e.g., walking in challenging environments. Different EF components, e.g., “working memory” (Holtzer et al., 2006), “divided attention” (Sheridan et al., 2003), and “inhibition” (Hausdorff et al., 2005), partly explain gait performance. Especially spatial and temporal dual-task cost characteristics of gait are associated with divided attention (de Bruin and Schmidt, 2010). Gait disturbances and fall events, caused by sensory and motor impairments, are believed to be moderated by executive functioning (Rapport et al., 1998; Scherder et al., 2011). Training of EFs in older adults might contribute to improved gait performance (Pichierri et al., 2012a) and might reduce fall events as EF performance predicted the risk for future falls (Mirelman et al., 2012). However, so far no direct cause and effect relationship was demonstrated between EF and gait (Yogev-Seligmann et al., 2008).

Anatomically, EFs have been linked with the frontal lobe of the brain, in particular the dorsolateral prefrontal cortex (PFC) and related brain networks (DeLong, 2000; Yogev-Seligmann et al., 2008). A large PFC volume and a greater PFC thickness were associated with better EFs (Yuan and Raz, 2014). During lifetime, the (pre) frontal network undergoes age-dependent neuronal changes; however, no consensus exists to the precise pattern of EF altering (Gunning-Dixon and Raz, 2003; Brickman et al., 2006; Yogev-Seligmann et al., 2008; Gunning-Dixon et al., 2009). One assumption is that the decline in frontal gray-matter might be associated with the deterioration of EFs (Zimmerman et al., 2006). Moreover, disturbances in cortico-cortical and cortico-subcortical connections, e.g., frontal connections with parietal lobes and basal ganglia, respectively, are classified as higher level gait disorders (Thompson and Nutt, 2007; Scherder et al., 2011). A phenomenon coined “retrogenesis” implies that brain circuits that mature late in ontogeny are most vulnerable to early neurodegeneration (Davis et al., 2009) and might contribute to the understanding and prediction of disturbances in higher level gait and gait-related motor activity. This suggestion is supported by recent work of Rosano et al. (2012) showing that a smaller volume of the prefrontal area is likely to contribute to slower gait through slower information processing (Rosano et al., 2012).

So far, training of cognitive abilities (e.g., EFs) may represent an important strategy to preserve brain function and also prevent mobility disability (de Bruin et al., 2011, 2013; Pichierri et al., 2012b; Rosano et al., 2012). Furthermore, recent reviews focusing on the interplay between physical function and cognition concluded that it seems important to combine motor and cognitive training into clinical practice to enable older adults to move safer in their physical environment (Segev-Jacubovski et al., 2011; Pichierri et al., 2012b; Bamidis et al., 2014). Especially, computerized interventions seem promising (Green and Bavelier, 2008; Pichierri et al., 2012b; Bamidis et al., 2014) when considering training principles that enhance (motor) learning (Green and Bavelier, 2008). Video games might have the potential to train cognitive functions (Zelinski and Reyes, 2009). A video game-based physical exercise, or a so-called exergame, allows the recommended combinatory training of motor and cognitive abilities. It is believed that physical exercise (PE) interventions with decision-making opportunities might facilitate the development of both motor performance and cognitive function (Yan and Zhou, 2009).

Recent research indicates that the effects of PE on the brain can be enhanced by concurrent consumption of natural products (van Praag, 2009). This means it can be hypothesized that a combination of physical training with a nutritional supplement (NS) has the potential to further enhance the effects of physical training on the level of brain structure and function in older persons. The potential synergy between nutrition and PE could involve common cellular pathways important for neurogenesis, cell survival, synaptic plasticity, and vascular function (van Praag, 2009).

A systematic review revealed that previous interventions using a combined approach of PE and NS to effect on the brain were not particularly successful because of the misfit between the combinations; the intervention components were not selected based on sharing of similar neuronal mechanisms (Schättin et al., 2016). The review indicates, however, that especially fish oil, containing omega-3 fatty acid (FA), might be an effective NS supporting the positive effects of PE. Omega-3 FA is important for energy metabolism and for the composition of the plasma membranes in the brain (Gómez-Pinilla, 2008). Another review showed that long chain polyunsaturated FA (LCPUFA) might improve cognition, decrease (neuro) inflammation, and reduce vascular risk factors in normal aging adults (Janssen and Kiliaan, 2014). Omega-3 LCPUFA may provide decreased brain deterioration through the positive effects on brain structure, function, and cerebral blood flow (Haast and Kiliaan, 2015). A recent randomized-controlled study showed that fish oil had positive effects on brain structure and function in healthy older adults (Witte et al., 2014). The participants showed improved EFs, white matter microstructure integrity, gray matter volume, and vascular parameters.

So far no study investigated the combined effect of exergame training and omega-3 FA on the elderly brain's structure and function. This study, therefore, aims to investigate the effects of a combination of exergame training and omega-3 FA. The following research question will guide through the research process: “Does the combination of exergame training and fish oil differently affect neuronal system levels in the elderly brain compared to exergame training alone?” The main objectives of the trial are (1) to determine the effects of the intervention on the neuronal structural level of the brain (neuronal excitability) and (2) to assess the effects on functional level in the brain (neuronal activity). We hypothesize that the combination will differently affect these parameters.

## Materials and methods

### Ethics and reporting

The study procedure has been approved by the local ethics committee (EC Zurich Switzerland, EC number: 2015-0190) and conforms to the Declaration of Helsinki and the guidelines of Good Clinical Practice E6 (R1). No data was recorded before written informed consent was given by the participants. The trial protocol follows the Consolidated Standards of Reporting Trials (CONSORT) statement on randomized trials of non-pharmacological treatment (Boutron et al., 2008) and Standard Protocol Items: Recommendations for Interventional Trials (SPIRIT) guidance for protocol reporting (Chan et al., 2013).

### Design and setting

The study is a randomized double-blinded, placebo-controlled study involving elderly adults above 65 years. The study is designed to examine the effect of omega-3 FA supplementation and exergame training on the endpoints of neuronal structure and function before and after a 26-weeks intervention period. The measurements and data collection, the exergame training, and data analysis are conducted at the same study site (ETH Hönggerberg, Zurich, Switzerland). At home, the participants are expected to take the NS regularly.

### Blinding, randomization, and allocation

The NS, packed in bottles equal in outer appearance, were blinded by an external center (Kantonsapotheke Zurich, Switzerland) to achieve double blinding. The external center created a computer-generated list including numbers from 001 to 060 that correspond to either fish oil or olive oil, respectively. The list number does not correspond to the participants' identification (ID) number. The list consists of six blocks of ten whereas fish oil and olive oil are randomly and equally distributed in all blocks. The investigators continuously assigned the volunteering women to the numbers starting with 001 and ending with 030 and the men starting with 031 and ending with 060. The randomization list is stored by a non-involved investigator and out of reach and sight of the involved investigators. For statistics, the groups will be referred to without specification of NS (e.g., group A and B).

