#### Nutritional supplementation

Participants randomized to the experimental group take a liquid (oily consistency) fish oil (San Omega AS, [name]). Participants randomized to the control group take olive oil as placebo (Oro del Desierto, [name]). The reasons for choosing olive oil as comparator are the similarity of taste, composition, consistency, and color. Thus, olive oil is the most commonly used placebo for omega-FA studies (Miller et al., 2014).

Over 26 weeks, the participants take a daily amount of 13.5 ml of fish oil, including 2.9 g of omega-3 FA, or 13.5 ml of olive oil. The first 16 weeks, the participants take the NS with the aim of reaching a steady state (Katan et al., 1997; Arterburn et al., 2006; Stonehouse, 2014). A review on omega-3 FA suggests that a duration of 16 weeks is needed to account for potential interaction effects of gender and age (Stonehouse, 2014). Moreover, the time frame of 16 weeks is the minimum time needed for red blood cells to reach a steady state (Katan et al., 1997; Arterburn et al., 2006). The duration and dosage of the omega-3 FA was based on findings of previous studies. Two studies showed no detectable cognitive benefits when considering an intake of 0.7 g for 24 months (Dangour et al., 2010) or 1.8 g for 26 weeks (van de Rest et al., 2014), respectively. A possible explanation might be that the dosage level is more important than the time frame. Witte et al. (2014) utilized 2.2 g for 26 weeks and achieved a significant increase of EF and beneficial effects in white-matter microstructure integrity and on gray-matter volume (Witte et al., 2014). A review identified low to moderate side effects in form of gastrointestinal upset, fishy aftertaste, worsening glycemia, and rise in low density lipoprotein cholesterol for 1–3 g/d of omega-3 FA (Kris-Etherton et al., 2003).

At home, the NS can be taken undiluted or can be added to food (e.g., salads) or drinks. At intervention start, the participants receive bottles including the NS, measuring cups (13.5 ml), and oral as well as written information about duration, dosage, and intake. To check for intake adherence, the participants are supplied with a NS diary including week days and daytime.

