### Statistics

The data analysis will be performed at the end of intervention including the measurement values from pre- and post-intervention measurements. Data will be tested for normal distribution using Shapiro-Wilk test and Q-Q-plots. A 2 × 2-ANOVA will be used with normally distributed data, the non-parametric equivalent for data not fulfilling assumptions of normal distribution. The test will be used to compare the two interventions over time (from pre- to post-measurement) on changes on the main dependent variables MEP, RRP, RT of cognitive tasks, spatio-temporal gait parameters, DTC, and FA levels. In addition to statistical significance testing effect size calculation (*r* = Z/√N) will be performed. The participants' FA blood levels, demographic, and health information will be examined in relation to the outcome measures in order to interpret the results in context. All statistical procedures will be conducted with the IBM Statistical Package for the Social Science software package. A probability level of *p* < 0.05 will be considered to be statistically significant.

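### Allocation is stratified by sex but the planned group-by-time ANOVA has no sex term, so the test is conservative if sex predicts the pre-to-post change

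*Protocol article*

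**What the plan says.** Under Blinding, randomization, and allocation, the protocol article describes a list of 60 numbers: "The list consists of six blocks of ten whereas fish oil and olive oil are randomly and equally distributed in all blocks". The investigators then "assigned the volunteering women to the numbers starting with 001 and ending with 030 and the men starting with 031 and ending with 060". The first three blocks are therefore for women and the last three for men. The article does not use the word, but this is stratification by sex.

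Under Statistics, the planned test is given as follows: "A 2 × 2-ANOVA will be used with normally distributed data, the non-parametric equivalent for data not fulfilling assumptions of normal distribution". Its purpose is to "compare the two interventions over time (from pre- to post-measurement) on changes on the main dependent variables MEP, RRP" and the remaining outcomes. The two factors are therefore group and time, and the treatment comparison is made on the pre-to-post change. Sex could enter only through the sentence that says "demographic, and health information will be examined in relation to the outcome measures in order to interpret the results in context", which describes an exploration for context and not a term in the model.

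Under Nutritional supplementation, a cited review is given as a reason for the 16-week run-in, namely to "account for potential interaction effects of gender and age".

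**The concern.** When allocation is forced into balance on a factor, that factor can no longer contribute to the difference between the arms. If the analysis leaves it out, any variation it explains in the analysed quantity still sits in the residual. The estimated standard error then overstates the real uncertainty, p-values are too large, confidence intervals are too wide, and the precision gained by stratifying is lost.

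The named model and the described randomisation do not match. A model with group, time and sex would not be a 2 × 2 ANOVA, and the non-parametric fallback is not described as stratified either. What is at stake is precision and power for both primary outcomes (MEP and RRP) and for the secondary ones. Validity in the sense of bias or false positives is not at stake.

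**Working it through.** The plan gives no figure on this point, so there is none to reproduce. Its sample-size figure does not enter the calculation.

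**Inputs**
- From the article: six blocks of ten, 1:1 within each block, three blocks per sex. If both strata fill, each sex has 3 × 5 = 15 participants per arm, so four cells of 15.
- From the article: the contrast is group × time, which with two time points is the comparison of mean change between the arms.
- Assumed, because the documents give nothing: a sex difference b in the mean change, the same in both arms, with b/σ between 0 and 1, where σ is the within-sex SD of change.

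**Step 1: sex shifts the level only.** If women and men differ by the same amount before and after, the difference drops out of each person's change. In a simulation with 20,000 trials per setting, 15 per cell and an assumed pre–post correlation of 0.6, the standard error of the group × time contrast was about 0.230 with or without sex. This held for level differences of 0.5, 1 and 2 SD. The ratio is 1.00, and type I error and power are unchanged.

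**Step 2: sex predicts the change.** With half of each arm from each sex, a sex difference b adds b²/4 to the within-arm variance, while the true sampling variance of the group difference still depends on σ² alone. Hence

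SE ratio k (without sex / with sex) = √(1 + b²/(4σ²)).

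The unadjusted test in effect rejects when the correctly scaled statistic exceeds 1.96 × k. In the normal approximation:
- two-sided type I error = 2 × [1 − Φ(1.96k)]
- power, for an effect that would have 80% with sex in the model (2.80 true standard errors) = Φ(2.80 − 1.96k)

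| b/σ | k | 1.96k | type I error | power |
|---|---|---|---|---|
| 0 | 1.000 | 1.960 | 5.0% | 80% |
| 0.25 | √1.0156 = 1.008 | 1.975 | 4.8% | 80% |
| 0.5 | √1.0625 = 1.031 | 2.020 | 4.3% | 78% |
| 0.8 | √1.16 = 1.077 | 2.111 | 3.5% | 76% |
| 1.0 | √1.25 = 1.118 | 2.191 | 2.8% | 73% |

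A cruder calculation, Φ(2.80/k − 1.96), ignores that the unadjusted statistic varies less than it should. It gives 78%, 74% and 71% at 0.5, 0.8 and 1.0. The last row is therefore best read as 71–73%.

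**Step 3: check by simulation.** With the same simulation, a sex effect on change of 0.5 and 1.0 outcome SD corresponds to b/σ = 0.56 and 1.12, since the SD of change is √(2 × (1 − 0.6)) = 0.894. The standard errors without and with sex were 0.239 and 0.230 (ratio 1.04), and 0.264 and 0.230 (ratio 1.15). The formula gives 1.038 and 1.146. Type I error without sex was 4.3% and 2.6%. With sex in the model it was about 5% in both settings.

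**The case against.** The strongest objection is that the planned contrast already removes most of what sex is likely to explain. MEP amplitude, reaction time and gait may well differ between women and men, and a reader might infer that any such difference inflates the standard error. Step 1 shows that it does not. A level effect would matter for a comparison of post values alone or for the group main effect, but the Statistics section makes neither of these the treatment contrast. This part of the objection stands, and it limits the point to sex effects on change.

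A second tempting reading is that the article expects sex to modify the response to omega-3. It does not say so. The remark under Nutritional supplementation reports a review, calls the interaction potential, gives no size, and serves to justify the 16 weeks. Moreover, if sex acted only through the response to fish oil, the average sex difference in change would be half the interaction. An average of 0.5 to 1.0 SD would then need an interaction of 1 to 2 SD, which is large.

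Third, the figures assume that both strata fill and that the cells stay equal. Drop-out, and the 70% attendance rule for the per-protocol analysis, need not preserve that. This qualifies the exact percentages but not the direction of the advice.

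Finally, the article is a condensed account, and a statistical analysis plan that is not shown could add covariates. That would excuse silence. Here the article names the model, and the named model has no place for sex.

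**Conclusion.** The point holds in a limited form. Allocation is stratified by sex and the stated analysis leaves sex out. The consequence is a conservative test, and only where sex predicts the pre-to-post change. For b/σ from 0 to 1 the standard error is 0 to 12% too large. The loss is negligible at 0.25, about two power points at 0.5, and seven to nine at 1.0. These sex effects are assumptions, and the documents do not show where in the range any outcome lies.

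The estimate of the treatment effect is not biased and false positives are not increased. The omission is worth correcting because the correction is nearly free and makes the analysis follow the randomisation. It is not a threat to the trial's validity.

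**What to change.** State in the Statistics section that sex was a stratification factor, and add sex and sex × time to the ANOVA for every outcome. For the treatment contrast this is the same as adding sex to a model of the change. If an ANCOVA of the post value on arm and baseline is used, add sex there. The point does not itself require a move to ANCOVA. Where the non-parametric route is taken, stratify the rank-based test of change by sex, for example with a van Elteren test. Fix this before the group codes are broken.

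The cost is one degree of freedom for the treatment contrast (with 60 participants, 60 − 2 = 58 becomes 60 − 3 = 57). No further data or participants are needed, and if sex is unrelated to change there is no measurable loss. Whether the effect of the oil differs by sex is a separate question that this term does not address.

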### Participants

Participants were recruited from the Senior's University Zurich (Switzerland), senior residency dwellings in Zurich (Switzerland), and through public advertisement. The public advertisement included a brief study description and study site contact information. All those who were interested received a study information sheet including the design, procedure, benefits, and risks of the study. Before the study procedure started, the participants had to provide signed written informed consent forms. Participants fulfilling all of the following inclusion criteria were eligible for the study: (1) age above 65 years, (2) live independently or in a residency dwelling, (3), non-smoker, and (4) healthy (self-reported). Participants were excluded if they exhibited one of the following exclusion criteria: (1) mobility impairments, (2) orthopedic or neurological diseases that prevent training participation, (3) rapidly progressive or terminal illness as well as acute or chronic illness, (4) history of heart attack, stroke, or epilepsy, (5) medication that interacts with NS (e.g., hypoglycemic medication and anticoagulants), (6) medication that acts on neuronal level (e.g., psychotropic medications), (7) cognitive impairment (Mini Mental Status Examination <22 points), (8) signs of an upcoming depression (Geriatric Depression Scale), (9) electronic or metallic head implants, and (10) personal history of dizziness.

